## PROTOCOL SYNOPSIS

|                              |                                                                                                                                                                                                                                                                                                                                                                                                                                                                                                                                                                                                                                                                                                                                                                                                                                                                                                                                                                                                                                                                                                                                                                                                                                                                                                                                                                       |
|------------------------------|-----------------------------------------------------------------------------------------------------------------------------------------------------------------------------------------------------------------------------------------------------------------------------------------------------------------------------------------------------------------------------------------------------------------------------------------------------------------------------------------------------------------------------------------------------------------------------------------------------------------------------------------------------------------------------------------------------------------------------------------------------------------------------------------------------------------------------------------------------------------------------------------------------------------------------------------------------------------------------------------------------------------------------------------------------------------------------------------------------------------------------------------------------------------------------------------------------------------------------------------------------------------------------------------------------------------------------------------------------------------------|
| TITLE                 | Comparison of Early Changes in Ocular Surface and Inflammatory Mediators between Lenticule Extraction and Small-Incision Lenticule Extraction                                                                                                                                                                                                                                                                                                                                                                                                                                                                                                                                                                                                                                                                                                                                                                                                                                                                                                                                                                                                                                                                                                                                                                                                                         |
| SPONSOR               | [name], PhD                                                                                                                                                                                                                                                                                                                                                                                                                                                                                                                                                                                                                                                                                                                                                                                                                                                                                                                                                                                                                                                                                                                                                                                                                                                                                                                                                 |
| FUNDING ORGANIZATIONS | National Natural Science Foundation of China (81371046)
Science and Technology Planning Project of Guangdong Province (2013B090200057)                                                                                                                                                                                                                                                                                                                                                                                                                                                                                                                                                                                                                                                                                                                                                                                                                                                                                                                                                                                                                                                                                                                                                                                                                             |
| RATIONALE             | 
This first all-in-one FS-laser system was designed to perform the refractive lenticule extraction (ReLEx) procedures, femtosecond lenticule extraction (FLEx) and small-incision lenticule extraction (SMILE). In FLEx, a corneal flap is created by the FS laser (similar to LASIK) and lifted, allowing lenticule removal[1-3]. For SMILE, a truly flapless procedure, only a small—2-4mm—incision is made, through which the lenticule is removed. Multiple etiologies contribute to this ocular surface disruption, including the flap creation and stromal ablation involved in previous refractive surgery techniques, such as: disable tear film, damage of the corneal nerve and postoperative inflammatory mediator. For both FLEx and SMILE, stromal ablation has been replaced by refractive lenticule removal. In terms of corneal flap formation, FLEx still requires an epithelial-stromal flap, while SMILE employs only a small incision to extract the lenticule. Hence, we hypothesize that SMILE will have less effect on patients' ocular surface markers and inflammatory mediators, compared to FLEx. To test our hypothesis, we conducted a prospective clinical study in patients who underwent FLEx or SMILE. Ocular surface parameters and inflammatory mediators were assessed and compared between the different types of surgery.
 |
| STUDY DESIGN          | This is a prospective, non-randomly study                                                                                                                                                                                                                                                                                                                                                                                                                                                                                                                                                                                                                                                                                                                                                                                                                                                                                                                                                                                                                                                                                                                                                                                                                                                                                                                             |
| PRIMARY OBJECTIVE     | Determine the changes of central corneal sensitivity, Schirmer I test (SIT), noninvasive tear breakup time (NI-TBUT), tear meniscus height, corneal fluorescein (FL) staining, ocular surface disease index (OSDI) and tear concentrations of interleukin-1 $\alpha$ (IL-1 $\alpha$ ), tumor necrosis factor- $\alpha$ (TNF- $\alpha$ ), nerve growth factor (NGF), interferon- $\gamma$ (IFN- $\gamma$ ), transforming growth factor- $\beta$ 1 (TGF- $\beta$ 1) and matrix metalloproteinase-9 (MMP-9) of the two surgeries preoperatively and postoperatively.                                                                                                                                                                                                                                                                                                                                                                                                                                                                                                                                                                                                                                                                                                                                                                                                     |
| SECONDARY OBJECTIVES  | Determine the correlation between inflammatory mediators and ocular surface changes.                                                                                                                                                                                                                                                                                                                                                                                                                                                                                                                                                                                                                                                                                                                                                                                                                                                                                                                                                                                                                                                                                                                                                                                                                                                                                  |
| NUMBER OF SUBJECTS    | 41 patients in total                                                                                                                                                                                                                                                                                                                                                                                                                                                                                                                                                                                                                                                                                                                                                                                                                                                                                                                                                                                                                                                                                                                                                                                                                                                                                                                                                  |

|                                                                |                                                                                                                                                                                                                                                                                                                                                                                                                                                                                                                                                                                                                                                                                                                                                                                                              |
|----------------------------------------------------------------|--------------------------------------------------------------------------------------------------------------------------------------------------------------------------------------------------------------------------------------------------------------------------------------------------------------------------------------------------------------------------------------------------------------------------------------------------------------------------------------------------------------------------------------------------------------------------------------------------------------------------------------------------------------------------------------------------------------------------------------------------------------------------------------------------------------|
| INCLUSION CRITERIA                                      | 
 
1. Minimum age of 18 years(range from 18 year to 25 years).
 
2. Corneal thickness more than 500 <math>\mu\text{m}</math> and calculated residual stromal bed after treatment greater than 300 <math>\mu\text{m}</math>.
 
3. Corneal thickness more than 500 <math>\mu\text{m}</math> and calculated residual stromal bed after treatment greater than 300 <math>\mu\text{m}</math>.
 
4. Preoperative cylindrical equivalent refraction between - 0.25 D and -1.50 D.
 
5. Preoperative corneal curvature from 41.0 D to 46.0 D with a regular topographic pattern.
 
6. monocular best corrected visual acuity of 20/20 or better and stable refractive error (less than 0.5 D change) for 24 months before surgery.
 
 |
| EXCLUSION CRITERIA                                      | 
 
1. Systemic disease that contraindicated the surgery (such as diabetes, glaucoma and systemic collagen vascular disease).
 
2. Corneal abnormality or disease.
 
3. A history of tear supplement usage.
 
4. Contact lens wear during the past year.
 
                                                                                                                                                                                                                                                                                                                                                                                                                                                                                  |
| GROUPS                                                  | 
Group 1: patients underwent FLEx surgery.
 
Group 2: patients underwent SMILE surgery.
                                                                                                                                                                                                                                                                                                                                                                                                                                                                                                                                                                                                                                                                                                |
| DURATION OF SUBJECT PARTICIPATION AND DURATION OF STUDY | 
Subjects will be on study for up to 2 months
 
Screening: 2-4weeks
 
Treatment: 1day
 
Follow-up: 1day, 1week and1month (1 month in total)
 
The total duration of the study is expected to be 9 months.
                                                                                                                                                                                                                                                                                                                                                                                                                                                                                                                                                                          |
| STATISTICS PLAN                                         | 
Data were analyzed using SPSS 19.0 software (SPSS, Chicago, IL, USA). Paired samples t-test (normally distributed data) or Wilcoxon test (non-normally distributed data) was used to determine significant differences between pre- and post-operative measurements in each group. Comparisons between the two groups were performed by Independent samples t-test (normally distributed data) or Mann-Whitney U test (non-normally distributed data). Pearson or Spearman rank correlation was used to analyzed for the correlations between tear inflammatory mediators and ocular surface parameters. P value of less than 0.05 was considered statistically significant. Data are presented as mean <math>\pm</math> SD.
                                                                   |

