## **2 STUDY RATIONALE**

This first all-in-one FS-laser system was designed to perform the refractive lenticule extraction (ReLEx) procedures, femtosecond lenticule extraction (FLEx) and small-incision lenticule extraction (SMILE). In FLEx, a corneal flap is created by the FS laser (similar to LASIK) and lifted, allowing lenticule removal[1-3]. For SMILE, a truly flapless procedure, only a small—2-4mm—incision is made, through which the lenticule is removed. Multiple etiologies contribute to this ocular surface disruption, including the flap creation and stromal ablation involved in previous refractive surgery techniques, such as: disable tear film, damage of the corneal nerve and postoperative inflammatory mediator. For both FLEx and SMILE, stromal ablation has been replaced by refractive lenticule removal. In terms of corneal flap formation, FLEx still requires an epithelial-stromal flap, while SMILE employs only a small incision to extract the lenticule. Hence, we hypothesize that SMILE will have less effect on patients' ocular surface markers and inflammatory mediators, compared to FLEx. To test our hypothesis, we conducted a prospective clinical study in patients who underwent FLEx or SMILE. Ocular surface parameters and inflammatory mediators were assessed and compared between the different types of surgery.

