## **3 STUDY OBJECTIVES**

### **3.1 Primary Objective**

3.1.1.Determine the changes of ocular surface including central corneal sensitivity, Schirmer I test (SIT), noninvasive tear breakup time (NI-TBUT), tear meniscus height, corneal fluorescein (FL) staining, ocular surface disease index (OSDI) of the two surgeries preoperatively and postoperatively

3.1.2.Evaluation the changes of tear concentrations of interleukin- $1\alpha$  (IL- $1\alpha$ ), tumor necrosis factor- $\alpha$  (TNF- $\alpha$ ), nerve growth factor (NGF), interferon- $\gamma$  (IFN- $\gamma$ ), transforming growth factor- $\beta 1$  (TGF- $\beta 1$ ) and matrix metalloproteinase-9 (MMP-9) of the two surgeries preoperatively and postoperatively.

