## **4 STUDY DESIGN**

This is a single center, prospective and non-randomly study. 41 patients are planned to be enrolled. They are divided into two groups. One group will undergo the FLEx surgery, the other group will undergo the SMILE surgery. The ocular surface parameters and concentration of tear inflammatory mediators will be assessed at baseline, 1 day,1 week and 1 month postoperatively. Subjects who meet all inclusion criteria and none of the exclusion criteria will be entered into the study.

1. Minimum age of 18 years(range from 18 year to 25 years).
2. Corneal thickness more than 500  $\mu\text{m}$  and calculated residual stromal bed after treatment greater than 300  $\mu\text{m}$ .
3. Corneal thickness more than 500  $\mu\text{m}$  and calculated residual stromal bed after treatment greater than 300  $\mu\text{m}$ .
4. Preoperative cylindrical equivalent refraction between -0.25 D and -1.50 D.
5. Preoperative corneal curvature from 41.0 D to 46.0 D with a regular topographic pattern.

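### The primary objective is worded as pre/post change of each surgery, so the planned SMILE-versus-FLEx test is not tied to it, and the scale of that test is not fixed

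*Protocol*

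**What the plan says.** - **Hypothesis (Protocol, 2 Study Rationale; repeated in the synopsis):** "we hypothesize that SMILE will have less effect on patients' ocular surface markers and inflammatory mediators, compared to FLEx". The same section adds that "Ocular surface parameters and inflammatory mediators were assessed and compared between the different types of surgery".
- **Title (synopsis):** "Comparison of Early Changes in Ocular Surface and Inflammatory Mediators between Lenticule Extraction and Small-Incision Lenticule Extraction".
- **Primary objective (3.1 and synopsis):** changes in six ocular surface measures and six tear mediators "of the two surgeries preoperatively and postoperatively". Neither this nor the secondary objective (a correlation) asks for a difference between the surgeries.
- **Statistics Plan (synopsis):** a paired t-test or Wilcoxon test "was used to determine significant differences between pre- and post-operative measurements in each group". The next sentence says "Comparisons between the two groups were performed by Independent samples t-test", or by Mann-Whitney U for non-normal data. A single threshold of 0.05 covers all tests.
- **Design (4 Study Design):** single centre, not randomised, 41 patients. "They are divided into two groups", with no group sizes given.

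**The concern.** The objective and the hypothesis call for different contrasts. Change after each surgery is a within-group question, answered by one paired test in FLEx and one in SMILE. Less effect after SMILE than after FLEx is a between-group question, answered only by comparing the groups. Each measure at each visit therefore yields three P-values at 0.05, and nothing says which of them carries the conclusion.

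This matters because the contrasts can disagree on the same data. A significant change after FLEx beside a non-significant one after SMILE is not a test of the difference between them. Whether a paired test reaches 0.05 also depends on how many patients are in that group, and the protocol does not state this.

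The between-group test has a gap of its own: the plan does not say which quantity it compares. In non-randomised groups that may already differ before surgery, post-operative values and changes from baseline can give different answers. All of this applies to a single measure at a single visit, so it is separate from the number of endpoints.

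**Working it through.** **Inputs from the protocol.** Total 41 patients; paired and between-group tests; threshold 0.05. There is no effect size, SD, power or group split, so the figure of 41 cannot be reproduced.

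**Assumptions.** Two-sided tests; normally distributed changes; the same true mean change *d* (in SD of change) in both groups; group sizes 20 FLEx/21 SMILE, with 15/26 and 26/15 as a range; one measure at one visit.

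**Step 1: paired test in one group.** Power is the probability that |T| exceeds the 0.975 quantile of t with n − 1 df, where T is noncentral t with noncentrality d√n. At d = 0.45 the noncentrality is 0.45 × √20 = 2.01 in FLEx and 0.45 × √21 = 2.06 in SMILE. The powers are 0.480 and 0.501.

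**Step 2: FLEx significant, SMILE not.** The groups are independent, so P = power(FLEx) × [1 − power(SMILE)]. At d = 0.45 this is 0.480 × (1 − 0.501) = 0.240.

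| d | Power FLEx (n = 20) | Power SMILE (n = 21) | FLEx only | Exactly one group |
|---|---|---|---|---|
| 0 | 0.050 | 0.050 | 4.8% | 9.5% |
| 0.2 | 0.136 | 0.141 | 11.7% | 23.9% |
| 0.3 | 0.247 | 0.258 | 18.3% | 37.8% |
| 0.45 | 0.480 | 0.501 | 24.0% | 50.0% |
| 0.6 | 0.721 | 0.744 | 18.5% | 39.2% |
| 0.8 | 0.924 | 0.936 | 5.9% | 13.0% |

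The last column includes SMILE-only results, which would not favour the hypothesis.

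**Step 3: unequal splits.** Over the values of d computed, the FLEx-only rate peaks as follows.
- 26 FLEx/15 SMILE, d = 0.5: 0.688 × (1 − 0.438) = 38.7%.
- 15 FLEx/26 SMILE, d = 0.4: 0.303 × (1 − 0.500) = 15.1%.

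**Step 4: the between-group t-test on change.** In 50,000 simulated trials at each of d = 0.3, 0.45 and 0.6 (20/21), it rejected in 5.0%, 5.0% and 5.1%. Among trials with the FLEx-only pattern, it was also significant in only 10 to 12%.

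**Step 5: power of that test at 20/21.** For a true difference δ in SD of change, the noncentrality is δ/√(1/20 + 1/21) = δ/0.312, with 39 df. Power is about 35% at δ = 0.5 and 70% at δ = 0.8, and it reaches 80% at δ of about 0.90.

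**Step 6: scale.** Let the groups differ by B before surgery and have the same true change. The expected difference in post-operative values is then B, while the expected difference in change is 0. The 5% in Step 4 therefore belongs to the test on change. A test on raw post-operative values would hold it only if B = 0, which a non-randomised design does not ensure.

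**The case against.** A reader might infer that the protocol names no between-group contrast, or that it will treat significance in FLEx alone as evidence for SMILE. The document supports neither reading. The sentence after the paired tests plans a between-group test. The title speaks of comparing changes between the procedures, and the rationale connects the hypothesis to a comparison between surgeries. No sentence gives discordant paired tests any comparative meaning, and being listed first does not make a test decisive. Paired tests are also a proper answer to an objective about change after each surgery. All of this stands, so the rates in Step 2 describe a misreading that the protocol leaves open, not a rule that it contains.

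The size of the problem also depends on assumptions. The inflation is confined to intermediate d: at 20/21 the FLEx-only rate is about 5% at d = 0 and 6% at d = 0.8. With the smaller group in FLEx it stays near 15% at most. The protocol supports no particular d or split.

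Finally, the SAP is not shown, and how within-group results are labelled or presented may be settled there. That does not excuse the objective: it is a protocol statement, and it does not ask the question that the hypothesis poses. The protocol also contains its own Statistics Plan, which gives the between-group test without its scale.

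**Conclusion.** The point holds in a limited form. The right family of test is planned, but the primary objective does not call for it, no priority separates it from the paired tests at the same 0.05, and its scale is open in a non-randomised comparison.

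If the paired tests were read side by side as a comparison, the false FLEx-only rate for one measure at one visit would run from about 5% to 24% at 20/21. Its maximum would be about 39% at 26/15 and about 15% at 15/26, against 5% for the between-group test on change. These figures rest on equal true change, normality, two-sided tests and assumed splits and values of d. This should be corrected before analysis; it does not show that the planned tests are invalid.

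**What to change.** In the synopsis objective, in 3.1 and in the Statistics Plan, state that the primary comparison is the SMILE-minus-FLEx difference in change from baseline, or alternatively in the post-operative value adjusted for baseline, with its 95% CI. Name one of the two in advance, because they can differ when the groups differ at baseline. Report within-group pre/post changes as descriptive estimates with 95% CIs, and state that they do not by themselves support a comparative claim.

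This needs no new data or visits. The cost is that the deciding contrast is less likely to reach P<0.05: at 20/21, about 35% power for a 0.5 SD difference, with 80% only at about 0.9 SD. Using change removes an additive baseline difference between the groups. It does not remove other confounding from non-randomised allocation, and it does not settle which measure or visit is primary.
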